### Methods in analysis to handle protocol non-adherence and any statistical methods to handle missing data {20c}

According to the methods described above, missing data will be reduced to a minimum. As for the primary outcome, imputations for missing data are not needed for a generalized mixed model. If missing data must be accounted for in the secondary outcomes, multiple imputation will be applied.

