### Additional consent provisions for collection and use of participant data and biological specimens {26b}

Consent includes the permission to collect whole blood, saliva for DNA extraction and for linkage to The Norwegian Registry of Persons Assessed for Cognitive Symptoms, the Norwegian Registry for Primary Health Care and the Norwegian patient registry. The additional consent for the glymphatic sub-study includes permission to collect plasma after spinal contrast injection.

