### Secondary outcomes

#### Clinical outcomes

Secondary cognitive endpoints are scores on tests within the working memory domain at 3, 6, 12, 24, and 48 months post intervention assessments. Moreover, secondary endpoints are the RBANS composite score, scores on the executive function domain, scores on the Mini-Mental State Examination (MMSE), the Clinical Dementia Rating scale (total and sum of boxes), and conversion to dementia.

We consider the participants as having dementia when they fulfill the National Institute on Aging and Alzheimer’s Association (NIA-AA) 2011 criteria for all-cause dementia [41]:

Cognitive or behavioral symptoms that:Hinder the ability to function independently in activities of daily living or workConstitute decrease in functioning and performing from previous levelsCould not be explained by delirium or a major psychiatric disorderCognitive impairment detected through history taking and cognitive testingInvolves at least two of the following domains:Immediate learning and delayed memory (list learning, story memory, list recall, list recognition, story memory and figure recall index score from RBANS test battery)Reasoning, judgement and handling of complex tasks (Clinical Dementia Rating Scale, CDR).Visuospatial abilities (figure copy and line orientation index score from the RBANS test battery)Language (picture naming and semantic fluency index score from RBANS test battery)Behavioral and psychological symptoms (Neuropsychiatric Inventory Questionnaire (NPI-Q), and Mild Behavioral Impairment Checklist (MBI-C))

We require age- and education-adjusted scores at least 1.5 SD below the mean to consider a cognitive domain as affected. Affected behavior requires a minimum of one domain with the severity score 2 (moderate) or 3 (severe) or a NPI-Q sum score ≥ 3. To ensure consistency, dementia diagnoses will be discussed in consensus meetings involving experienced geriatricians and neuropsychologists.

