#### Use of health care resources and health economics (work package 4)

A cost-utility analysis will be performed to evaluate if the working memory training is more cost-effective compared to the active control group in the MCI phase. The generic outcome in the analysis is QALYs derived from the instrument EQ-5D 5L. The secondary outcome is productivity loss of relatives and patients.

The use of QALY as a patient-reported outcome measure in dementia research is debated, as concerns arise regarding patients’ potential unawareness of their impairments or difficulty accurately reporting their status due to memory limitations. The health economic analysis will therefore include the following costs:Intervention-related costsDirect costs/health care costs, mainly related to the use of health care services, including primary, secondary and tertiary care and health servicesIndirect costs, including work absence for the patients and the relatives of the patients (i.e., productivity loss).

Data will be collected through self-report measures (EQ-5D 5L) and from the Norwegian patient registry. Informal care will be measured by interviews with the family using Resource utilization in dementia [42].

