### Plans to promote participant retention and complete follow-up {18b}

Detailed information about the study set-up and requirements will be sent to the participants before inclusion and the importance of completion will be stressed. Participants can stop the training or withdraw consent at any time without providing a reason to discontinue. In case of training cessation, the participants will be asked, but are not obliged, to complete the follow-up assessments. To promote retention, all participants will be coached during the training period, regardless of study group allocation. The research nurses remind patients of MRI and study-visit appointments, and we aim to coordinate the MRI examinations on the same day as the study visit.

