## Statistical methods

### Statistical methods for primary and secondary outcomes {20a} and subgroup analyses {20b}

Baseline characteristics and other descriptive data will be summarized using appropriate descriptive statistics. Continuous variables will be described using the mean and standard deviation, or the median and interquartile range, as appropriate based on the distribution. Categorical variables will be described using counts and percentages. Simpler parametric or non-parametric comparisons may be used for descriptive or supplementary analyses.

The main analytical framework for longitudinal primary and secondary outcomes will be regression-based repeated-measures analyses, primarily using linear mixed-effects models (LMEs) (and generalized mixed-effects models for non-continuous outcomes, where relevant). These models account for within-participant correlation over time and allow inclusion of participants with incomplete follow-up data under standard model assumptions. Analyses of intervention effects will include time, treatment group, and the time × treatment group interaction as key terms. Relevant covariates (e.g., age, sex, and baseline values), as appropriate for the specific outcome, will be included in adjusted analyses. Given the heterogeneity of disease severity in MCI and risk of baseline imbalance in a moderate sample size, if systematic baseline differences are observed across the groups, a multidimensional composite covariate may be developed and included as an adjustment variable.

Planned contrasts will include comparisons of the single-training group and double-training group versus the active-control group at 6 months as the main outcome. If the double-training group is significantly better than the active-control group at 6 months, the estimated mean difference between the double-training and single-training groups will be tested at the 5% significance level to assess a possible dose–response effect. Pairwise contrasts between groups will also be estimated at 3 and 12 months to assess immediate and longer-term effects. Multiple comparisons will be applied using Holm–Bonferroni across the relevant tests. Results will include estimated marginal means with 95% confidence intervals, mean difference between groups with 95% CIs, and standardized effect sizes (Cohen’s *d* derived using the pooled baseline standard deviation).

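### Conversion to dementia falls under a general multiple-imputation rule for missing secondary outcomes, while registry linkage that consent already covers is given no stated role in finding diagnoses among participants who stop attending

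*Protocol article*

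**What the plan says.** **Missing-data rule.** Section {20c} treats the two classes of outcome differently. For the primary: "As for the primary outcome, imputations for missing data are not needed for a generalized mixed model". For the rest: "If missing data must be accounted for in the secondary outcomes, multiple imputation will be applied". The second sentence makes no distinction by outcome or by reason for missingness.

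**Main models.** Section {20a} puts mixed models first, with "generalized mixed-effects models for non-continuous outcomes, where relevant", and says that these models "allow inclusion of participants with incomplete follow-up data under standard model assumptions". It lists a tipping-point analysis among sensitivity analyses that may be done.

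**The endpoint.** Conversion to dementia is listed under Secondary outcomes, Clinical outcomes. It applies the NIA-AA 2011 criteria using RBANS indices, the CDR and behavioural scales, and "dementia diagnoses will be discussed in consensus meetings involving experienced geriatricians and neuropsychologists". No other source of the diagnosis is described.

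**Registries.** Consent (section {26b}) includes "linkage to The Norwegian Registry of Persons Assessed for Cognitive Symptoms, the Norwegian Registry for Primary Health Care and the Norwegian patient registry". The analytic use stated for registry data is economic: the work package 4 outcome section names the patient registry, and the last paragraph of {20a} describes merging national registry data with questionnaires.

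**Retention.** Section {18b} says: "In case of training cessation, the participants will be asked, but are not obliged, to complete the follow-up assessments". This concerns people who stop training. No section says how outcome data are obtained once visits stop.

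**The concern.** Delaying progression is the motive given in the abstract and background, and conversion to dementia is the secondary outcome closest to it. Participants who are declining are plausibly the ones who find a test battery and travel hardest, so absence at a late visit may carry information about the outcome. Multiple imputation in its usual form, and a likelihood-based mixed model, are valid only if the missingness can be explained by data already recorded.

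The visit schedule strains that condition. Nothing is scheduled between months 24 and 48, so for someone absent at month 48 the latest trial information is two years old. By the protocol's own projection, close to half of all conversions arise in that interval.

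Meanwhile the trial holds consent to look for a recorded diagnosis. Modelling an unobserved diagnosis is a weaker choice than looking it up where that can be done.

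**Working it through.** **Inputs, all from Sample size {14}:** 213 participants; 10% dropout; 9.6% annual transition to dementia; 39 and 71 projected cases at 24 and 48 months.

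**1. Reproduce the projection.** Cases = N × (1 − (1 − r)^t).
- 24 months: 213 × (1 − 0.904²) = 213 × 0.183 = 38.9, matching 39.
- 48 months: 213 × (1 − 0.904⁴) = 213 × 0.332 = 70.7, matching 71.

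**2. Share arising after month 24.** 71 − 39 = 32, and 32/71 = 45%.

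**3. Conversions among leavers, on the protocol's figures.** Leavers: 213 × 0.10 = 21.3.
- All lost from baseline, same risk as the others: 21.3 × 0.332 = 7.1. This is the upper bound at equal risk.
- All lost just after the 24-month visit: 21.3 × (0.332 − 0.183) = 3.2.

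At equal risk, then, about 3 to 7 conversions would be unobserved, depending on when people leave.

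**4. Departures from those figures (assumptions).**
- Leavers convert at twice the annual rate, lost from baseline: 1 − 0.808⁴ = 0.574, and 21.3 × 0.574 = 12.2. The other 191.7 participants give 191.7 × 0.332 = 63.7, so this is about 12 of 76.
- The 10% is attached to the sample size for the 6-month primary outcome; loss by 48 months could be higher. At equal risk, 20% loss from baseline gives 213 × 0.20 × 0.332 = 14.1 and 30% gives 21.2, of about 71.

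**5. What imputation would supply.** If leavers convert at twice the rate, a model that used no post-baseline information would impute about 7 conversions where about 12 occurred. One that used earlier RBANS, MMSE and CDR results would close part of that gap. The documents do not allow the remainder to be quantified.

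**The case against.** **The rule is conditional and mixed models come first.** Both true. A reader might infer that conversion and QALYs are certain to be imputed; the text does not say so. But a mixed model does not avoid the difficulty, because it rests on the same kind of ignorability assumption and does not supply the missing diagnosis.

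**Informative loss is provided for.** A tipping-point analysis is mentioned, but only as an option, in a paragraph that opens with the primary analysis. It would show how sensitive a result is; it would not recover events.

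**Imputation need not ignore decline.** This stands. A good imputation model would use earlier scores, and choosing that model is ordinary SAP content. It would be wrong to say that imputation assumes the whole of the informative loss away.

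**Registry diagnoses are a different endpoint.** This stands too. They are not NIA-AA diagnoses reached by consensus, and the article says nothing of the registries' coverage, criteria or timeliness. Mixing sources according to attendance could misclassify unevenly if attendance differs by arm. Hence the panel review, source flag and visit-only analysis proposed below.

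**The article does not exclude registry use for conversion.** Correct: the consent wording does not limit the purpose. The point is that no such use is stated, while a different method for the same gap is.

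**Dead participants and QALYs.** Work package 4 says: "The generic outcome in the analysis is QALYs derived from the instrument EQ-5D 5L". Since QALYs also sit under Secondary outcomes, a reader might infer that participants who die would be imputed EQ-5D values and credited with QALYs. The documents do not support that reading. They do not say how outcomes are handled after death, and setting utility to zero from death is ordinary practice that a health-economic plan would cover.

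**Bias between arms.** A reader might also infer differential loss from the different lengths of coaching. Nothing in the article shows it.

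**Conclusion.** The point holds as a weak analysis choice for one important secondary outcome. It is not an error of arithmetic or a contradiction. As written, where missing conversion status must be dealt with, the stated method is imputation, although consent already permits linkage that might supply a diagnosis.

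On the protocol's own figures, up to about 7 of 71 projected conversions at 48 months are at issue. That bound assumes every leaver is lost from baseline and converts at the same rate as the others; with later loss it is nearer 3. The larger figures, 12 at a doubled rate and 14 to 21 at 20% to 30% loss, rest on assumptions. That loss is related to conversion is plausible but not demonstrated here, and the direction and size of any bias in the treatment comparison cannot be derived from the article. The 6-month primary outcome is untouched.

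**What to change.** In the Clinical outcomes section and in {20c}, state that for participants who stop visits without withdrawing consent to linkage:

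- registry dementia diagnoses and their dates will be obtained;
- the blinded consensus panel will review them and record the source of each diagnosis;
- the reviewed result will be used for conversion status, and as auxiliary information in any imputation model;
- conversion established from visits alone will be a sensitivity analysis.

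As a clarification only, add that the imputation rule does not apply after death, with EQ-5D utility taken as 0 from the date of death.

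The cost is wording, diagnosis and date fields in the registry linkage already planned for work package 4, and panel time. The contents of that extract are not described, so the fields and registries needed should be checked, as should coverage. The downside is less uniform ascertainment than the consensus endpoint. There is time to do this: the last baseline assessment was expected in April 2025, which puts the last 48-month visit at about April 2029.

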### Plans to give access to the full protocol, participant level-data, and statistical code {31c}

Restrictions imposed by the ethical committee prevent publicly sharing de-identified data. Data may be requested from the corresponding author according to research collaboration and data transfer guidelines. Availability is dependent on approval from The Norwegian regional committee for medical and health research ethics (REC).

## Oversight and monitoring

### Composition of the coordinating center and trial steering committee {5d}

The project-running group (Principal Investigator, postdoctoral fellow MRI, postdoctoral fellow glymphatics, postdoctoral fellow cognition, PhD candidates, and study secretary) oversees the project and meets monthly. Regularly, the wider team including the research nurses at the study centers meet 2–4 times a year. Both the advisory board and the User representative board meets with the Principal Investigator 2–3 times a year throughout the trial.

### Composition of the data monitoring committee, its role, and reporting structure {21a}

No DMC is established for the REACT MCI study based on the low-risk intervention in a non-critical population.

### Adverse event reporting and harms {22}

Computerized working memory-training programs might be tiresome but involve no harm to the participants. The craniospinal clearance investigation (glymphatics sub-study) is explorative in nature, and participants can opt out of inclusion to this sub-study. Moreover, there is a strict protocol in place regarding eligibility in this study arm. Although invasive in nature, the procedure is associated with minimal risk for participants. Any harm to participants will be registered in the trial database, and reported through the local institutions adverse events system.

### Plans for communicating important protocol amendments to relevant parties (e.g. trial participants, ethical committees) {25}

Changes to the protocol require the project-running group to seek permission from the Regional Ethics Committee.

### Dissemination plans {31a}

The results will be disseminated by scientific papers submitted to peer-review medical journals. Authorship will be determined based on the Vancouver criteria, and a written agreement regarding ownership of data and publications are signed by all project group members. The dissemination of study results will also be aimed at the general public by the www.reactmci.no website, social media such as Facebook and X, soft science publications and talks, and by using the networks within the patient and user organizations.

## Discussion

Currently, effective therapy for MCI is lacking. This multi-center randomized controlled trial assesses whether working memory training (20–25 sessions over 5 weeks) can improve cognitive function after 3, 6, 12, 24, and 48 months. Additionally, we will examine the microstructural effects of working memory training using MRI and explore the potential for identifying high responders by analyzing associations with glymphatic system function and genetic variations. Finally, we will evaluate the impact of working memory training on quality of life, caregiver stress, and its cost-effectiveness in individuals with MCI. Finding an intervention postponing the progression of MCI is of great importance for patients as well as for the global economy and health care. Moreover, identification of markers for training effects is important for future personalized interventions.

The 5-week working-memory training intervention leverages patients’ own resources, which is underexplored in MCI [28]. Most studies in the MCI-dementia continuum focus on disease modification or pathogenesis, with patient-centered outcomes like quality of life (QoL) and caregiver burden often underrepresented despite their importance to patients and caregivers [45]. Even small improvements or stabilization in health-related QoL (HRQoL) can be significant to the individual and thus provide cost-effective care.

To our knowledge, no studies have examined the effects of cognitive training interventions on caregivers. MCI impacts not only the affected individual but also caregivers, who report high levels of stress and, in some cases, depression or anxiety [46, 47]. The relationship between cognitive decline, neuropsychiatric symptoms, and caregiver burden is bidirectional [48]. Strengthening the ability of individuals to remain at home is crucial, especially in light of demographic changes.

Furthermore, this study gives insight in the socioeconomic impact of MCI in the Norwegian population, including hidden costs for the participants’ relatives. These data are currently unavailable in Norway.

This study challenges current practice in MCI by utilizing computer-based working memory training. Moreover, we aim to fill knowledge gaps regarding the length of training, the personalization of this intervention, as well as the effect on quality of life, caregiver stress, and its cost-effectiveness.

## Trial status

The trial started in May 2021. The current protocol is version 3.02 (dated 03/04/2024). Clinical trial identifier: NCT04792528. Last baseline assessment is expected in April 2025.

## Data Availability

Access to data will be governed by a written agreement between all participating centers and regulated by the Norwegian Regional Committee for Medical and Health Research Ethics (REK).
